### Stopping criteria

Participants will be informed that they can withdraw their consent at any time during the trial without affecting their healthcare and without needing to give a reason. If participants decide to withdraw, the primary reason for discontinuation will be determined and recorded where possible. Individuals will be informed that, should they withdraw, the data collected to that point cannot be erased and may still be used in final analyses.

### Nested qualitative interviews

Semistructured interviews will be conducted with patients, HCPs (eg, consultants, physiotherapists, nurses, occupational therapists), and researchers to explore their perceptions of the proposed stratification tool. Findings from the interviews will determine the tool’s acceptability and feasibility and inform any necessary refinements to the tool’s procedure based on participants’, HCPs’ and researchers’ experiences. The interview schedules for participants, HCPs and researchers (onlinesupplemental materials 3  4) will be informed by the Extended Normalisation Process Theory^90 91^ and our public contributors to develop an understanding of how the proposed tool may be implemented within healthcare practices. All interviews will be audio-recorded with consent via Microsoft Teams or a Dictaphone, either online, face-to-face or by telephone, based on the individual’s preference. Recordings will be transcribed verbatim, and any identifiable information will be removed.

Participants will be purposively sampled initially, with theoretical sampling later to explore emerging themes. Approximately 27 participants, 22 HCPs and researchers will ensure that perspectives across all conditions—gender, age, ethnicity, social deprivation, job role and career level—are represented (table 2). Participants will be individuals who have experienced the new tool as part of the study. HCPs and researchers will be recruited via Cwm Taf Morgannwg University Health Board, Sherwood Forest NHS Foundation Trust, Primary Integrated Community Services, social media, word of mouth and advertising through the British Pain Society. All HCPs and researchers will be provided with an invitation letter, participant information sheet and e-consent (online supplemental material 5) to complete if interested. Topics may include the proposed utility and feasibility of the assessments for the tool, including challenges and barriers and how it may fit into clinical practice, patient burden, any unexpected or undesirable side effects experienced, attitudes and behaviours towards the tool, overall experience and any previous experience with pain assessment tools. The development of interview questions may be iterative and informed by early interviews, with later interviews incorporating additional questions and each round exploring themes from previous rounds in greater depth. One-to-one interviews will be conducted by researchers with appropriate experience in qualitative research.

**Table 2 T2:** Sampling framework and the number of participants for each characteristic

Participants	Subpopulations	What we need	Sample	Total sample
Patients with musculoskeletal conditions	Osteoarthritis	Male: Female 2:4 Age (40–65, >65 years) Socioeconomic+ethnic variation	6	27
	Inflammatory arthritis	RA, PSA, axSpA, 3:3:3 Male: Female 1:2 (RA), 1:1 (PSA), 2:1 axSpA Age (18–39, 40–65, >65 years) Socioeconomic+ethnic variation	9	
	Fibromyalgia	Male: Female 2:4 Age (18–39, 40–65, >65 years) Socioeconomic+ethnic variation	6	
	Chronic low back pain	Male: Female 2:4 Age (18–39, 40–65, >65 years) Socioeconomic+ethnic variation	6	
Researcher	Early career researcher		2	4
	Metrologist/research nurse		2	
Healthcare professionals	Pharmacist	Community vs NHS	2	18
	Physiotherapist	Pain specialist vs no specialist Early vs established	4	
	Occupational therapist	Pain specialist vs no specialist Early vs established	4	
	Nurse	Pain specialist vs no specialist Early vs established	4	
	Rheumatologist/consultant	Early vs established	2	
	General practitioner	Early vs established	2	

axSpA, axial spondylarthritis; NHS, National Health Service; PSA, psoriatic arthritis; RA, rheumatoid arthritis.

Interviews will take place within 1 week of participants’ experience with the stratification tool to ensure accurate recall. They may be conducted face-to-face in a private room, by phone or online via Microsoft Teams, at the interviewee’s discretion. For HCPs, researchers and participants requiring follow-up interviews, short videos of the stratification tool will be provided before the interview. The HCPs and researchers will be recruited through primary and secondary care, via social media and through connections with relevant gatekeepers and the research team.

### Data management

The collection, storage, processing and disclosure of personal information, along with data management, will comply with the requirements of the General Data Protection Regulation 2018. Data handling will adhere to the Sponsor (University of Nottingham) and study sites’ policies and procedures. All personal data will be anonymised, and any further data analysis will be conducted without reference to personally identifiable information. The sponsor will oversee the conduct of the trial.

### Sample size

A sample size of 250 participants at baseline, with an anticipated 200 individuals completing the follow-up questionnaires, accounting for 20% attrition.^92^ Provides additional statistical power and robustness to detect differences, allowing for more precise estimates of interactions and better management of potential missing data, therefore enhancing the validity of our findings.

Rasch measurement theory (RMT) to determine the structural validity of the risk stratification tool assumes that item calibrations lie within ±½ logit of stable values within a 99% CI, resulting in an overall sample size between 108 and 243, from best to poor targeting.^93 94^ This aligns with the Consensus-based Standards for the selection of health Measurement Instruments recommendations RMT analysis.^95^

Pain profiles will be identified irrespective of condition, using multivariate models with 5 covariates, 95% power and an effect size of 0.5 would require 236 individuals to complete baseline assessments.^51^ For longitudinal modelling, assuming a correlation coefficient of 0.15 with 12-week pain, 164 participants with α=0.05 and 95% power.

Interviews will be conducted until theoretical saturation, the point at which additional data do not reveal any new themes that achieve conceptual depth.^96^ It is anticipated that 27 interviews will be conducted with participants and 22 HCPs and researchers (table 2).

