### Outcomes

Primary outcomes:

The risk for persistent pain or pain worsening to a clinically important extent, using the risk stratification tool (combined clinical QST and CAP).Sensitivity and specificity of the risk stratification tool to identify people at risk of persistent and/or worsening pain.

Secondary outcomes:

External validity of the risk stratification tool against laboratory QST and validated questionnaires addressing central sensitisation-related characteristics.Internal validity of the risk stratification tool.Pain prognosis: Prediction of pain at 12 weeks by the risk stratification tool, CAP and clinical QST separately.Mechanistic underpinning: Investigate, according to the assessments outlined, which pain mechanisms contribute to risk levels identified using the risk stratification tool.Acceptability and feasibility of the risk stratification tool by patients, healthcare professionals (HCPs) and researchers within both research and clinical environments.Refinement of the risk stratification tool by patients, HCPs and researchers.Inter-rater and intrarater reliability of the risk stratification tool.

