### Data analysis

Pain profiling will be undertaken irrespective of condition. Multivariate modelling (principal component analysis, cluster analysis or latent class analysis) to identify distinct pain patterns.Between-group comparisons (eg, independent T-tests, Mann-Whitney U) will explore between pain profile comparisons.Associations between pain profiles and clinical outcomes (eg, pain intensity, pain-related worrying, disability, quality of life) will be examined.Sensitivity analysis will be conducted between diagnostic groups and between matched samples.We believe that QST will identify somatosensory pain profiles, while CAP will identify psychological hypervigilance pain profiles, each associated with augmented central pain processing. Using the pain profiles combined with pain at 12 weeks, we will identify any relationship between potential augmented central pain processing and pain prognosis at 12 weeks (eg, persistent/worsening pain, pain>patient acceptable symptom state), informed by patterns of pain over 12 weeks and knowledge.Pain prognosis: Bivariable correlations will identify and permit comparison between baseline factors significantly associated with 3-month pain prognosis. Separate multivariable models will determine whether the CAP questionnaire, clinical QST or laboratory QST can increase prognostic precision beyond other clinical and demographic variables significantly associated with pain prognosis. Multivariable modelling will define whether and which combination of the CAP questionnaire and QST importantly improves prognostic determination. The proportion of the prognosis explained by each and by both the CAP questionnaire and clinical or laboratory QST will be determined.The reliability and validity of the stratification tool (combined CAP and clinical QST) will be tested across the study population, with sensitivity analysis conducted across the diagnostic groups, age, sex, social and ethnic strata.Test–retest reliability will be assessed using intraclass correlation between repeated CAP questionnaires and between two raters for simplified clinical QST.RMT, Cronbach’s alpha and confirmatory factor analysis will evaluate internal validity, consistency and factor structure. If multiple constructs with significant residual values exist, this will be further explored using principal component analysis of residuals, the eigenvalue criterion, residual correlations and theoretical understanding.Correlation analysis will assess external validity against self-reported questionnaires and laboratory QST.Mechanistic underpinning: The dataset will be randomly divided into development and validation sets. Exploratory and confirmatory factor analyses will determine whether there are subgroups of the population for whom the stratification tools function differently. Correlations between CAP scores and clinical and laboratory QST indices of augmented central pain processing will be identified. Bivariate and multivariable models will ascertain whether associations may be explained by one or more characteristics linked to maladaptive pain processing (sleep disturbance, fatigue, anxiety, depression, cognitive impact, catastrophising).Relevance to patient-centred outcomes: Bivariate associations between CAP or QST and patient-reported outcome measures scores will be determined through linear regression. The proportion of participant-reported pain or other patient-reported outcome measures explained by CAP scores, clinical and/or laboratory QST measures, will be identified as R^2^ in multivariable regression.Qualitative data will be analysed using reflexive thematic analysis following the stages outlined by Braun and Clarke.^97^ A reflexive journal will be kept throughout the data collection process. Data will be coded inductively primarily, while also being informed by the Normalisation Process Theory^90 91^ commonly used to support evaluation in health interventions and inform the tool’s theoretical acceptability and feasibility. A ‘critical friend’^98^ will code a sample of transcripts independently until consensus is reached. After the consensus is reached, all remaining transcripts will be coded. NVivo V.15 will assist in managing, analysing, and visualising the qualitative data set. A thematic map may also visually represent the main themes developed.

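### The only follow-up sample-size calculation (r = 0.15, 164 participants) does not give its stated 95% power and does not address the primary sensitivity and specificity outcome

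*Protocol article*

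**What the plan says.** The Sample size section of the protocol article plans for 250 recruited and 200 followed up: "A sample size of 250 participants at baseline, with an anticipated 200 individuals completing the follow-up questionnaires, accounting for 20% attrition". It then gives three size bases.

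- Rasch analysis of the tool's structure: "resulting in an overall sample size between 108 and 243, from best to poor targeting". This concerns item calibration, not follow-up pain.
- Pain profiles: "95% power and an effect size of 0.5 would require 236 individuals to complete baseline assessments". This is explicitly a baseline analysis.
- Follow-up: "For longitudinal modelling, assuming a correlation coefficient of 0.15 with 12-week pain, 164 participants with α=0.05 and 95% power". This is the only basis that involves 12-week pain. It does not say which predictor has the correlation, or whether the test is one- or two-sided.

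The Outcomes section lists two primary outcomes. One is the risk of persistent or importantly worsening pain as given by the combined tool. The other is "Sensitivity and specificity of the risk stratification tool to identify people at risk of persistent and/or worsening pain". No target value, null value, cut-off or expected outcome rate accompanies it.

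Under pain prognosis, the Data analysis section plans bivariable correlations and then models that ask what each part adds: "Multivariable modelling will define whether and which combination of the CAP questionnaire and QST importantly improves prognostic determination".

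**The concern.** Two things do not fit. First, 164 is small for detecting a correlation of 0.15 with 95% power, so the statement may fail on its own inputs. Second, a correlation with 12-week pain is a different quantity from the sensitivity and specificity of a tool that calls people positive or negative, and from the gain of a combination over one of its parts.

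At stake is how the results are read. A reader who sees 200 completers against a requirement of 164 will take the follow-up analyses to have more than 95% power. If they do not, a non-significant correlation or increment carries much less information than the section implies.

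**Working it through.** **1. The plan's own figure.** Inputs from the Sample size section: "assuming a correlation coefficient of 0.15 with 12-week pain" and "164 participants with α=0.05 and 95% power". For one correlation, Fisher's z gives N = ((z_alpha + z_power)/atanh(r))² + 3, with atanh(0.15) = 0.1511.

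- Two-sided: ((1.960 + 1.645)/0.1511)² + 3 ≈ 572.
- One-sided: ((1.645 + 1.645)/0.1511)² + 3 ≈ 477.
- Even 80% power needs 347 two-sided or 274 one-sided.

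So 164 is not reproduced. In the other direction, power = Φ(atanh(r)·√(N − 3) − z_alpha), where the opposite tail is negligible:

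| N | 0.1511 × √(N − 3) | two-sided | one-sided |
|---|---|---|---|
| 164 | 1.918 | 48% | 61% |
| 200 | 2.121 | 56% | 68% |

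The correlation that 164 supports at 95% power is tanh(3.605/√161) ≈ 0.28 two-sided, or tanh(3.290/√161) ≈ 0.25 one-sided.

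Other readings of 0.15 were tried. As Cohen's f² in an overall regression F test, 95% power needs 160 participants with 8 predictors and 166 with 9. As R², it needs 162 with 13 and 167 with 14. These come close to 164, but the text calls 0.15 a correlation coefficient and gives none of these predictor counts.

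**2. Gain of the combination over CAP alone.** Assumptions: CAP and clinical QST each correlate r with 12-week pain, and correlate ρ = 0.1 to 0.4 with each other. Then R² = 2r²/(1 + ρ), and the effect size for adding QST to CAP is f² = (R² − r²)/(1 − R²). It is tested by a 1-df F test with noncentrality N·f², two-sided 0.05, N = 200.

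- r = 0.15, ρ = 0.4: R² = 0.0321, f² = 0.0100, noncentrality 1.99, power 29%.
- r = 0.15, ρ = 0.1: R² = 0.0409, f² = 0.0192, noncentrality 3.84, power 50%.
- r = 0.25, ρ = 0.4 to 0.1: f² = 0.029 to 0.058, power 67% to 92%.

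**3. Sensitivity and specificity.** The documents state no test, so one has to be assumed: a two-sided Wald test that sensitivity + specificity exceeds 1, at 200 completers with 30–85% having the outcome. Where r is the input, tool score and pain are taken as bivariate normal with the tool cut at its median.

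Worked case, r = 0.15 and 50% with the outcome:

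- Sensitivity = specificity = 0.5 + arcsin(0.15)/π = 0.548.
- The standard error of their sum is √(2 × 0.548 × 0.452/100) = 0.070.
- z = 0.096/0.070 ≈ 1.36, so power is about 28%.

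| Assumed truth | Power at 200 |
|---|---|
| tool's r = 0.15 | 20–28% |
| tool's r = 0.28 (what 164 supports, two-sided) | 58–73% |
| 0.15 meant as f², so R = √(0.15/1.15) ≈ 0.36 | 83–93% |
| sensitivity = specificity = 0.65 to 0.70 | about 89–100% |

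**4. Precision at 200 completers.** The 95% half-width is 1.96·√(p(1 − p)/m), where m is the number with the outcome (for sensitivity) or without it (for specificity). For p = 0.70:

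- 50% prevalence: m = 100 and 100, giving ±9 and ±9 points.
- 85% prevalence: m = 170 and 30, giving ±7 and ±16 points.

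**The case against.** The strongest reply is that the follow-up calculation was never attached to sensitivity and specificity. With no null value, target, cut-off or outcome rate stated, power for that outcome is undefined. This stands. A reader might infer that power for the primary outcome is far below 95%, but the documents do not support that: it is low only if the tool's association with pain is as weak as 0.15 to 0.28. If true sensitivity and specificity are 0.65 to 0.70, then 200 completers give about 89% or more.

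A reader might also infer that the planning effect describes a classifier barely better than chance. That assumes 0.15 belongs to the whole tool, which the text does not say. If each part has r = 0.15, the combination in step 2 has R of about 0.18 to 0.20. Steps 2 and 3 therefore apply r to different things and should not be read as one scenario.

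It can also be said that longitudinal modelling need not mean a single correlation, and that 164 sits between the f² = 0.15 sizes for 8 and 9 predictors. That is a plausible origin for the figure, but the words on the page say otherwise. If it is the origin, the statement still needs correcting.

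Finally, the article condenses a fuller protocol, so finer detail may be given there. That covers matters left out. It does not cover a printed power figure that its printed inputs contradict.

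**Conclusion.** The follow-up sample-size statement is wrong as written. For a single correlation of 0.15 it delivers 48% two-sided power at 164 and 56% at 200, not 95%. That result uses only the protocol's own inputs and the standard test of one correlation.

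For the combination against CAP alone, power at 200 is about 29–50% if each part has r = 0.15, and 67–92% if 0.25. This depends on equal contributions from the two parts and an assumed CAP–QST correlation of 0.1 to 0.4.

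For the primary sensitivity and specificity outcome, the supportable conclusion is narrower: none of the three size bases addresses it, and its power depends entirely on an effect the document does not state. That is a gap in justification. It does not show that 200 completers are too few. The attrition arithmetic is sound (250 × 0.8 = 200), and nothing here requires a larger study.

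**What to change.** Keep 250 recruited and 200 followed up, and change the Sample size section in two places.

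1. Withdraw the 95% power claim for longitudinal modelling. Replace it with what 200 completers give, naming the effect measure and sidedness. For a single correlation, two-sided 0.05, the detectable r is tanh(3.605/√197) ≈ 0.25 at 95% power and tanh(2.802/√197) ≈ 0.20 at 80%. Alternatively, state the 56% power at r = 0.15. If 0.15 was meant as f² or R², say so and give the number of predictors. Do not keep 164 as the requirement for r = 0.15. For the question of what the combination adds, state the detectable increment or its power, with the assumed CAP–QST correlation.

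2. Justify the sensitivity and specificity outcome by expected precision: the 95% half-width for each at 200 completers over an assumed prevalence range. For a true value of 0.70, this runs from ±9/±9 points at 50% prevalence to ±7/±16 at 85%.

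The cost is a rewritten paragraph, with no added participants or assessments. The downside is that the published figures become less favourable than those now stated.

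### The longitudinal sample size does not follow from its inputs: for a correlation of 0.15, 164 participants give about 48% power (two-sided), and 95% power needs about 570

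*Protocol article*

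**What the plan says.** The Sample size section of the protocol article sets the target as follows: "A sample size of 250 participants at baseline, with an anticipated 200 individuals completing the follow-up questionnaires, accounting for 20% attrition". It then gives separate justifications for the Rasch analysis (108 to 243), for the baseline pain profiles ("using multivariate models with 5 covariates, 95% power and an effect size of 0.5 would require 236 individuals") and for the longitudinal modelling: "assuming a correlation coefficient of 0.15 with 12-week pain, 164 participants with α=0.05 and 95% power".

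The longitudinal statement gives the effect measure, its size, alpha, power and N. It does not give sidedness, a number of predictors, or the variance explained by covariates; the 5 covariates belong to the pain-profile calculation.

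The matching analysis is under Data analysis: "Bivariable correlations will identify and permit comparison between baseline factors significantly associated with 3-month pain prognosis". Multivariable models follow, which ask whether CAP and QST add prognostic precision.

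**The concern.** A correlation of 0.15 explains only 2.25% of the variance (0.15² = 0.0225). Showing so weak an association with 95% power normally takes several hundred participants, so 164 looked too small.

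This is the only power statement tied to 12-week pain. Prediction of persistent or worsening pain appears under the primary objective, and the risk of such pain is the first primary outcome. The planned modelling also carries forward clinical and demographic variables according to whether they are significantly associated with prognosis, so low power affects model building as well as the final tests. A reader who trusts 95% power at r = 0.15 would take a non-significant CAP or QST association as good evidence that none of that size exists.

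**Working it through.** **Inputs (protocol article, Sample size).** r = 0.15; alpha = 0.05; power = 95%; stated N = 164; expected completers = 200; enrolled = 250. Sidedness is not stated, so both versions are shown.

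**Attempt to reproduce 164 (Fisher z).** N = ((z_alpha + z_power) / atanh(r))² + 3, with atanh(0.15) = 0.1511.

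- Two-sided, 95% power: ((1.960 + 1.645) / 0.1511)² + 3 = 571.9, so 572.
- One-sided, 95% power: ((1.645 + 1.645) / 0.1511)² + 3 = 476.8, so 477.
- 80% power: 347 two-sided, 274 one-sided.

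The noncentral t (point-biserial) calculation gives 567 two-sided and 472 one-sided for 95% power. The stated 164 is not reproduced. It falls short even of 80% power one-sided, and an allowance for attrition would only raise the requirement.

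**Power at the available sizes.** Power = Φ(atanh(r) × √(n − 3) − z_alpha).

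- n = 164, two-sided: Φ(0.1511 × 12.69 − 1.960) = Φ(−0.042) = 0.483.
- n = 200, two-sided: Φ(0.1511 × 14.04 − 1.960) = Φ(0.161) = 0.564.

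| n | Two-sided | One-sided |
|---|---|---|
| 164 | 48% | 61% |
| 200 (expected completers) | 56% | 68% |
| 250 (no attrition) | 66% | 77% |

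Noncentral t gives 49% and 61% at n = 164, and 57% and 69% at n = 200.

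**Detectable correlation, two-sided.** r = tanh((z_alpha + z_power) / √(n − 3)).

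- n = 200, 95% power: tanh(3.605 / 14.04) = 0.251.
- n = 200, 80% power: tanh((1.960 + 0.842) / 14.04) = 0.197.
- n = 164, 95% power: tanh(3.605 / 12.69) = 0.277.

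**Where 164 might have come from.** None of these readings is stated in the article.

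- Correlation of 0.25, one-sided, 95% power: 164 exactly by noncentral t, 169 by Fisher z.
- 0.15 as Cohen's f² for a whole regression model: 160 with 8 predictors, 166 with 9.
- 0.15 as R²: 162 with 13 predictors, 167 with 14.
- 0.15 as a multiple correlation (R² = 0.0225): 865 with 5 predictors, so further away.
- 0.15 as a semipartial correlation: 95% power needs noncentrality of about (1.960 + 1.645)² = 13.0, so f² = 13.0 / 164 = 0.079. The residual variance would then be 0.0225 / 0.079 = 0.28, meaning the model explains about 72% of the variance in 12-week pain.

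**The case against.** The strongest reply is that 0.15 is a mislabelled Cohen's f². That fits the word modelling and the planned multivariable analyses. With 8 or 9 predictors, 164 would give about 95% to 96% power and 200 about 98% to 99%, so the N could stand and only the label would change. This is possible, but no whole number of predictors returns 164, and the article calls the figure a correlation coefficient. On this reading too the printed sentence is wrong. The objection does stand against claiming to know the cause: the one-sided 0.25 match is exact but remains an inference, and the fix has to allow for another measure.

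Three further points bear on the consequence.

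- Sidedness is unstated, so 48% is conditional on a two-sided test. That is true, but one-sided power is only 61%.
- The error did not set the enrolment target: 250 covers both the Rasch upper figure of 243 and the 236 for pain profiles. That stands, and it is why no change in recruitment is asked for.
- The link to the primary outcome is loose. Outcomes lists prediction of pain at 12 weeks as secondary, a correlation does not power sensitivity and specificity, and the article nowhere says that non-significant results will be read as no association. This partly stands: over-interpretation is a risk, not a stated plan. But Objectives places 12-week prediction under the primary objective as well as the secondary ones, and no other power figure covers it.

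**Conclusion.** The concern holds. On the stated inputs, N is too small by a factor of about 3.5 (572 / 164) two-sided, or about 2.9 (477 / 164) one-sided. At r = 0.15 the 200 expected completers would miss a real association about 44% of the time (1 − 0.564) two-sided, against the 5% that the article implies. Even the full 250 without attrition would not reach 95% power.

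These figures assume a single correlation tested against zero at alpha 0.05, which is the natural reading of the sentence and matches the planned bivariable correlations. If another effect measure was meant, the size of the error changes, but the sentence still needs correcting because it names a correlation of 0.15.

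**What to change.** Remove the claim that 164 participants give 95% power for r = 0.15, and state what the design delivers. Suggested wording: *With 200 completers and two-sided alpha 0.05, the study has 95% power to detect a correlation with 12-week pain of about 0.25, 80% power for about 0.20, and 56% power for 0.15.*

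If the sponsor's records show that 0.15 was a different measure, such as Cohen's f² for a multivariable model, name that measure, give the number of predictors and the sidedness, and recompute N from them.

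Add that non-significant prognostic associations will be interpreted through their confidence intervals and not as evidence of no association.

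The cost is a sentence or two in the protocol or SAP and a less favourable power figure, with no extra participants. The article gives April 2027 as the expected end of the study, so the correction can be made before analysis.
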